## Abstract

**Background:**

In diabetic patients a predisposed coronary microcirculation along with a higher risk of distal particulate embolization during primary percutaneous intervention (PCI) increases the risk of peri-procedural microcirculatory damage. However, new antiplatelet agents, in particular Ticagrelor, may protect the microcirculation through its adenosine-mediated vasodilatory effects.

**Methods:**

PREDICT is an original, prospective, randomized, multicenter controlled study designed to investigate the protective effect of Ticagrelor on the microcirculation during PCI in patient with diabetes mellitus type 2 or pre-diabetic status. The primary endpoints of this study aim to test (i) the decrease in microcirculatory resistance with antiplatelet therapy (Ticagrelor > Clopidogrel; mechanistic effect) and (ii) the relative microcirculatory protection of Ticagrelor compared to Clopidogrel during PCI (Ticagrelor < Clopidogrel; protective effect).

**Conclusions:**

PREDICT will be the first multicentre clinical trial to test the adenosine-mediated vasodilatory effect of Ticagrelor on the microcirculation during PCI in diabetic patients. The results will provide important insights into the prospective beneficial effect of this drug in preventing microvascular impairment related to PCI (http://www.clinicaltrials.gov No. NCT02698618).

**Electronic supplementary material:**

The online version of this article (doi:10.1186/s12933-017-0543-5) contains supplementary material, which is available to authorized users.

## Background

Type 2 diabetes mellitus (T2DM) is associated with a significant increase in the risk of coronary artery disease. As the prevalence of diabetes is estimated to double in the next 10 years, the burden of cardiovascular disease associated with this condition will dramatically increase. Although, over the last two decades, cardiovascular mortality has declined considerably in the general population, a similar trend has not been observed amongst diabetic patients [1]. This might be partly explained by the fact that diabetic patients have poorer outcomes than their non-diabetic counterparts [2, 3], both acutely and at long term follow up after coronary revascularization [4]. One of the mechanisms that may be related to this inferior outcome is the higher prevalence of periprocedural myocardial infarction (PMI) after percutaneous coronary intervention (PCI) observed in diabetic patients, which has been associated with endothelial dysfunction, pro-thrombotic state, chronic microvascular dysfunction, increased atheroma burden, vessel wall inflammation, and development of vulnerable plaques prone to distal embolization [5].

New antiplatelet agents, in particular Ticagrelor, might play a protective role in this setting. Ticagrelor, is different to Clopidogrel and other P2Y_12_ inhibitors, as it reduces the physiological clearance of adenosine by inhibiting its cellular uptake, thus increasing the plasma concentration of adenosine. As the primary aim of adenosine is achieving tonic and cellular protection during stress conditions [6], adenosine in turn may protect the myocardium from both ischemic and reperfusion injuries via its potent vasodilator effect and possibly by anti-inflammatory and antiplatelet properties [7].

Additionally, previous research [8] has identified a more pronounced effect of adenosine on microcirculatory resistance in patients with obesity and diabetes. Therefore, a potentially higher protective effect of Ticagrelor during PCI might be expected in this subgroup.

The PREDICT trial was therefore designed to investigate the potential protective effect of Ticagrelor on the coronary microcirculation during PCI in stable T2DM patients.

## Rationale

Coronary plaques at high risk for distal embolization during PCI [such as those with a thin cap fibroatheroma (TCFA)] are more prevalent in patients with T2DM [5]. Thus, this population is at high risk for developing myocardial injury and microcirculation impairment after PCI.By blocking the ENT1 nucleoside cell membrane transporter, Ticagrelor inhibits cellular uptake of adenosine and thus its physiological clearance, increasing the circulating levels of adenosine. Adenosine may protect the myocardium from both ischemic and reperfusion injuries via its potent vasodilator effect and/or through its anti-inflammatory and antiplatelet properties [7]. Physiologically this may be recognized as a more pronounced decrease in coronary microvascular resistance induced by adenosine after the administration of Ticagrelor [9].Previous research from our group [8] has suggested a more profound vasodilatory effect of adenosine on the microcirculation in patients with obesity and diabetes; these patients may have a greater protective benefit from Ticagrelor during PCI.

Therefore, Ticagrelor may be superior to Clopidogrel in providing microcirculatory protection during PCI procedures in patients with T2DM or pre-T2DM (primary hypothesis). Onset of treatment prior to PCI with Ticagrelor may be followed by a beneficial reduction in coronary microcirculatory parameters, as compared to Clopidogrel (secondary hypothesis).

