## Methods

### Trial design and objectives

The PRotective Effect on the coronary microcirculation of patients with DIabetes by Clopidogrel or Ticagrelor (PREDICT) trial (http://www.clinicaltrials.gov No. NCT02698618) is a prospective, multicenter, randomized, open-label study designed to investigate the protective effect of Ticagrelor over Clopidogrel on the coronary microcirculation during PCI in patients with T2DM or pre-T2DM. The primary endpoint aims to document (i) a decrease in coronary microcirculatory resistance caused by treatment onset (Ticagrelor > Clopidogrel; mechanistic effect) and (ii) a lower increase in microcirculatory resistance caused by PCI (Ticagrelor < Clopidogrel; protective effect). A detailed list of endpoints is reported in Table 1 and defined in the Additional file 1: Appendix. A dedicated eCRF platform will be designed and hosted in the http://www.cardiogroup.org website.

**Table 1 Tab1:** Study endpoints

Primary
Decrease in microcirculatory resistance caused by treatment onset (Ticagrelor > Clopidogrel)—*mechanistic effect*
Increase in microcirculatory resistance caused PCI (Ticagrelor < Clopidogrel)—*protective effect*
Secondary
Myocardial necrosis associated with PCI damage, assessed by cardiac biomarkers^a^
Absolute resistance value after PCI
Incidence of severe microcirculatory impairment defined as IMR > 29 after PCI
Subgroups analysis
Obese subjects

*PCI* percutaneous coronary intervention

^a^Third universal definition of myocardial infarction [40]

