## Sample size and statistical analysis

As no studies are currently available reporting on the impact of Ticagrelor on microvascular function compared to Clopidogrel, we based our sample size calculation on a previous study [10] showing that the intracoronary administration of Nicorandil after PCI resulted in a difference of 10 units in deltaIMR with respect to the control group. Assuming a difference of 10 in deltaIMR, in the experimental vs. control group, and a standard deviation of 10 a total of at least 20 patients per group would be needed to achieve an 80% power at a 2-sided alpha of 0.025, which accounts for the multiple primary endpoint design with a Bonferroni correction. Therefore, we aim to enroll 25 patients per group in order to take into account a 25% of potential missing data or major protocol violation due to clinical reasons (for example: clinical instability of patient between index and PCI procedure leading to urgent revascularization before completion of the protocol).

Any subject who took no trial medication will be eliminated from the full analysis set. Although a low or null proportion of exclusions due to treatment non-compliance is expected, any potential biases arising from this exclusion will be addressed. Imputation techniques will be used in an attempt to compensate for missing data. Regarding missing data, for primary endpoints, listwise deletion will be used meanwhile for the rest of analyses, listwise deletion or multiple imputation will be considered, depending on the type of missing process and on the quantification of the efficiency loss due to case deletion in each case. An investigation will be made concerning the sensitivity of the results of analysis to the method of imputation, especially if the number of missing values is substantial.

Being PREDICT a multicenter trial, the influence of the centre on the treatment effect and other endpoints will be addressed, and further adjustment will be done in the subsequent analysis, if necessary. Special attention will also be paid to the role of baseline measurements of the primary variable and diabetes treatment. Moreover, obese patients and those with previous myocardial infarction are subgroups of interest and their influence on the primary variables will be addressed and interpreted. However, subgroup analyses here have a exploratory nature, and therefore, interpreted cautiously.

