## Discussion

The main purpose of the PREDICT trial is to test if Ticagrelor provides greater protection to the coronary microcirculation during PCI in diabetic patients compared to Clopidogrel as assessed by microvascular resistance indices. The results will provide important insights into the prospective beneficial effect of this drug in preventing microvascular impairment related to PCI. In the following paragraphs, we briefly discuss the rationale behind our study hypothesis.

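### The Rationale calls the treatment-onset effect the secondary hypothesis, but the endpoints and sample size make it one of two primaries at alpha 0.025; reconcile the two and name the correction (Holm)

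*Protocol article*

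**What the plan says.** The Rationale states two ranked hypotheses. The first is superiority of ticagrelor in "microcirculatory protection during PCI procedures in patients with T2DM or pre-T2DM (primary hypothesis". The second concerns starting treatment before PCI, which may bring a "beneficial reduction in coronary microcirculatory parameters, as compared to Clopidogrel (secondary hypothesis".

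Other sections do not keep this ranking:

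- **Abstract, Methods:** "The primary endpoints of this study aim to test (i) the decrease in microcirculatory resistance with antiplatelet therapy", with protection during PCI as item (ii).
- **Trial design and objectives:** "The primary endpoint aims to document (i) a decrease in coronary microcirculatory resistance caused by treatment onset", again with protection as item (ii).
- **Table 1:** the first entry under the primary heading is "Decrease in microcirculatory resistance caused by treatment onset (Ticagrelor > Clopidogrel".
- **Sample size and statistical analysis:** the trial is sized to "achieve an 80% power at a 2-sided alpha of 0.025", "which accounts for the multiple primary endpoint design with a Bonferroni correction". The analysis text later in that section says that p values will be corrected for the multiple endpoint, but it names no method there.

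The Discussion gives the main purpose as "to test if Ticagrelor provides greater protection to the coronary microcirculation during PCI in diabetic patients". It does not mention the treatment-onset effect when it says so.

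**The concern.** The rank of an endpoint decides how much alpha it receives and what the trial may claim. Suppose the mechanistic comparison has p below 0.025 and the protective comparison has p above 0.05. Under Table 1 and the Bonferroni split, this is a positive result on a primary endpoint. Under the Rationale, the primary hypothesis has not been shown and only a secondary one is supported. If the conflict remains when the data are seen, whichever endpoint came out well can be presented as the primary one, with a passage of the article to support it.

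The second question is which correction will be applied. If the Bonferroni split used for sizing is carried into the analysis, some rejections are given up that a step-down procedure would allow at the same familywise error rate.

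**Working it through.** **Rankings side by side**

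| Place | Treatment-onset effect | Protection during PCI |
|---|---|---|
| Rationale | secondary hypothesis | primary hypothesis |
| Abstract, Methods | primary (i) | primary (ii) |
| Trial design, Table 1 | primary, listed first | primary |
| Sample size | alpha 0.025 each, Bonferroni over multiple primaries | same |
| Discussion | not mentioned in the statement of purpose | main purpose |

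Only the Rationale puts the treatment-onset effect second, and no section reconciles it with the rest.

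**Inputs** (Sample size and statistical analysis): difference 10 in deltaIMR, SD 10, two-sided alpha 0.025, power 80%, 20 per group needed, 25 per group enrolled, 25% allowance for loss.

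**The plan's own figure.** Normal approximation: n = 2·SD²·(z₁₋α/₂ + z₁₋β)²/δ² = 2·100·(2.241 + 0.842)²/100 = 19.01, so 20 per group. The stated 20 is reproduced. The noncentral t calculation gives 20.3, with 79.3% power at 20.

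**Evaluable number used below.** 25 × (1 − 0.25) = 18.75, taken as 19 per group.

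**Bonferroni against Holm.** Bonferroni rejects each endpoint at p ≤ 0.025. Holm rejects the smaller p value at ≤ 0.025 and, if that succeeds, the larger at ≤ 0.05. They differ only when one p value is at most 0.025 and the other lies between 0.025 and 0.05. So Holm rejects everything that Bonferroni rejects. The chance of at least one rejection is the same under both, and the gain is all on the second endpoint.

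Simulation with t tests, 19 per group, SD 10 and a 10-unit effect on both endpoints. The documents give no correlation between the two changes, so it is an assumption shown as a range. A negative value is plausible because the pre-PCI IMR enters the two benefits with opposite signs.

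| Correlation | Per endpoint, Bonferroni → Holm | Both endpoints, Bonferroni → Holm |
|---|---|---|
| −0.5 | 77% → 84% | 55% → 70% |
| 0 | 77% → 83% | 59% → 72% |
| +0.5 | 77% → 82% | 64% → 75% |

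The sample size section gives one 10-unit difference and does not say which endpoint it belongs to, so the mechanistic effect was also reduced. Power for the protective endpoint at correlation −0.5, Bonferroni to Holm:

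- mechanistic effect 5 units: 77.2% to 79.8%. The gain is about 2 points at correlation 0 and about 1 point at +0.5;
- 2.5 units: 76.8% to 77.7%;
- none: 76.7% to 76.8%.

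**If the Rationale ranking were adopted.** Protection would be tested first at 0.05. Noncentral t, difference/SD = 1:

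| Evaluable per group | alpha 0.025 | alpha 0.05 | Difference |
|---|---|---|---|
| 19 | 76.8% | 85.1% | 8.3 points |
| 20 | 79.3% | 86.9% | 7.6 points |
| 25 | 88.5% | 93.4% | 4.9 points |

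**The case against.** The strongest reply is that the operative text is consistent. The Abstract, the design section, Table 1 and the sample size all describe two primary endpoints, and the analysis text promises a matching correction. The exception is a parenthetical label in a narrative section, and changing it alters neither alpha nor sample size. This largely stands, and it is why the fix starts from that label. It does not remove the conflict, because the label sits on an explicit statement of the trial's hypotheses.

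Four stronger readings are tempting, and the documents do not support them.

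- A reader might infer that the Discussion also ranks the mechanistic effect second. It states a main purpose and ranks nothing, and a main purpose is compatible with two primaries.
- A reader might infer that the Bonferroni split wrongly costs the protective endpoint about 8 points of power. That compares the plan with a single-primary design that the Methods did not adopt. The trial was openly sized at 0.025, Bonferroni is valid, and the loss is the price of a second primary endpoint. It is also smaller, 4.9 points, if all 25 per group are evaluable.
- A reader might infer that the analysis is tied to Bonferroni. That method is named only for sizing. The promise to correct p values names none, so Holm already fits it.
- A reader might infer that Holm is a large gain at no cost. The larger figures need a 10-unit effect on both endpoints. The article also promises confidence intervals where possible, and simultaneous intervals that match Holm are less simple than those that match Bonferroni.

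**Conclusion.** The contradiction is real and in the current text: the same effect is a secondary hypothesis in the Rationale and a primary endpoint, with its share of alpha, elsewhere. What is at stake is the definition of a primary success. The familywise error rate is not at risk, since the Bonferroni split controls it, and the stated 20 per group is reproduced.

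Naming Holm is a modest further improvement. Under the plan's assumptions applied to both endpoints, with 19 evaluable per group, it adds about 5 to 7 points per endpoint (77% to 82–84%) and about 11 to 15 points for winning on both (64% to 75% and 55% to 70%). For the protective endpoint alone the gain depends on a mechanistic effect being present, and it nearly vanishes without one. These figures rest on SD 10 for both changes, t tests and an assumed correlation between −0.5 and +0.5.

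**What to change.** Before outcomes are known:

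1. In the Rationale, call both hypotheses primary, in line with the Abstract, Table 1 and the sample size section. State that success on either endpoint after correction is a primary result.
2. In the analysis text of the sample size and statistical analysis section, name Holm's step-down at a familywise two-sided 0.05 as the correction for the two primary p values.
3. Keep 0.025 in the sample size calculation as a conservative sizing alpha. The calculation itself need not change.
4. State how confidence intervals for the two primaries will be reported, for example Bonferroni-level intervals beside Holm-adjusted p values, noting that the two may occasionally disagree.

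This costs wording only, with no additional patients.

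If the sponsor instead means the Rationale ranking, the coherent alternative is a fixed sequence: protection at two-sided 0.05, then the mechanistic effect at 0.05 only if protection is significant. Table 1, the Abstract, the design text and the sizing alpha would then have to change. The price is that no confirmatory mechanistic claim is possible if protection fails. That choice belongs to the sponsor.

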## Methods

### Trial design and objectives

The PRotective Effect on the coronary microcirculation of patients with DIabetes by Clopidogrel or Ticagrelor (PREDICT) trial (http://www.clinicaltrials.gov No. NCT02698618) is a prospective, multicenter, randomized, open-label study designed to investigate the protective effect of Ticagrelor over Clopidogrel on the coronary microcirculation during PCI in patients with T2DM or pre-T2DM. The primary endpoint aims to document (i) a decrease in coronary microcirculatory resistance caused by treatment onset (Ticagrelor > Clopidogrel; mechanistic effect) and (ii) a lower increase in microcirculatory resistance caused by PCI (Ticagrelor < Clopidogrel; protective effect). A detailed list of endpoints is reported in Table 1 and defined in the Additional file 1: Appendix. A dedicated eCRF platform will be designed and hosted in the http://www.cardiogroup.org website.

**Table 1 Tab1:** Study endpoints

Primary
Decrease in microcirculatory resistance caused by treatment onset (Ticagrelor > Clopidogrel)—*mechanistic effect*
Increase in microcirculatory resistance caused PCI (Ticagrelor < Clopidogrel)—*protective effect*
Secondary
Myocardial necrosis associated with PCI damage, assessed by cardiac biomarkers^a^
Absolute resistance value after PCI
Incidence of severe microcirculatory impairment defined as IMR > 29 after PCI
Subgroups analysis
Obese subjects

*PCI* percutaneous coronary intervention

^a^Third universal definition of myocardial infarction [40]

### Population recruitment and flow chart

The inclusion and exclusion criteria are listed in Table 2. The target population consists of patients with T2DM or pre-T2DM with stable ischemic heart disease and a single vessel stenosis or multiple vessels with single stenoses technically amenable to PCI and pressure wire study.

**Table 2 Tab2:** Study inclusion and exclusion criteria

Inclusion criteria
Subject with type 2 diabetes mellitus or pre-type 2 diabetes mellitus status^a^
Subject must be older than 18 years
Written informed consent available
Documented silent ischemia, stable angina or patient who is scheduled for elective revascularization
Subject is eligible for PCI, and PCI target(s) have FFR ≤0.80
Exclusion criteria
Prior myocardial infarction in the territory of the target vessel
Akinesia or dyskinesia in subtended myocardial segments
Severe impairment of left ventricular function (LVEF <35%)
PCI target is a chronic total occlusion
Target lesion has been treated previously (restenotic lesions)
Target vessel is a saphenous vein graft or a surgical graft has been anastomosed to the target vessel
TIMI flow ≤1 prior to guide wire crossing
Subject is not eligible for treatment with drug eluting stent
Bleeding disorders or chronic anticoagulant treatment
Left main stenosis >50%
Coronary surgery deemed more beneficial for the patient than PCI
Ongoing treatment with Ticagrelor
Intolerance or contraindications to anti-platelet drugs
Contraindications for adenosine administration
Platelet count <75,000 or >700,000/mm^3^
Pregnant or breast feeding patient
History of intracranial hemorrhage
Severe hepatic impairment

*FFR* Fractional Flow Reserve, *LVEF* Left Ventricular Ejection Fraction, *PCI* percutaneous coronary intervention, *TIMI* thrombolysis in myocardial infarction

^a^2014 American Diabetes Association definition [41]

The study will be conducted as follows (Fig. 1, flow chart):

**Fig. 1 Fig1:**
[figure not shown]
Study flow chart. *CFR* coronary flow reserve, *IMR* Index of Microvascular Resistance, *FFR* Fractional Flow Reserve, *AMI* acute myocardial infarction, *PCI* percutaneous coronary intervention, *CK*-*MB* creatine kinase myoband, *cTn I* cardiac troponin I

Patient identification and enrollment: All consecutive patients with stable ischemic heart disease and T2DM or pre-T2DM referred for coronary angiography will be screened as potentially eligible for the study. Assessment of coronary stenosis severity using Fractional Flow Reserve (FFR) and the status of the microcirculation including measurement of coronary flow reserve (CFR) and Index of Microvascular Resistance (IMR) [10, 11] will be performed with the same pressure guidewire as part of the diagnostic process. Revascularization will be considered whenever a FFR ≤0.80 is found in a stenosis amenable to PCI. Eligible patients requiring PCI will be informed of the characteristics of the study and invited to participate.Randomization: Patients will be randomly assigned (1:1 ratio) to receive either Clopidogrel (600 mg loading dose followed by a daily dose of 75 mg) or Ticagrelor (180 mg loading dose followed by a dose of 90 mg b.i.d). The groups will be balanced according to the presence or absence of obesity [12] (Body Mass Index ≥ 30 kg/m^2^) [12] with the implementation of a dedicated randomization list. Patients who are already on oral treatment with Clopidogrel 75 mg/day are allowed to enter the protocol. According to randomization arm these patients will be assigned, after baseline assessment of microcirculation, to continue Clopidogrel 75 mg/day or be switched to Ticagrelor (180 mg loading dose followed by a dose of 90 mg b.i.d).PCI procedure: PCI procedure will be deferred for at least 48 h after the first administration of the study drug treatment in order to allow approximately 5 mean-half life times of their active metabolites, similar to a previously published study [9].3.1.Pre-PCI: Multimodal physiological evaluation (FFR, CFR, IMR) will be repeated.3.2.PCI: For all patients undergoing PCI, unfractioned heparin will be administered at the time of PCI. The PCI procedures will be performed using standard techniques using and second generation Drug Eluting Stents. Balloon pre-dilatation will be mandatory before stent implantation using a semi-compliant balloon with a diameter smaller than 75% of the distal reference vessel size in order to avoid confounding effects related to pre-dilation [13]. Post-dilation will be performed according to clinical practice although it will not be mandatory. All PCI characteristics (materials and techniques) will be recorded.3.3.Post-PCI: After stent implantation, multimodal intracoronary physiological evaluation will be repeated (FFR, CFR, IMR).
In-hospital stay: High-sensitivity cardiac troponin and creatine kinase myoband (CK-MB) will be determined in blood samples taken after the intervention (8 and 24 h in all cases, and every 24 up to 72 h in case of rising myocardial markers).In-hospital follow-up and data acquisition: Major adverse cardiac events as well as any bleeding complications occurring during in-hospital stay will be recorded (see Additional file 1: Appendix). All data required to test the primary and secondary endpoints will be collected before hospital discharge.Length of participation: Patients will terminate their study participation at the time of hospital discharge.

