A diagram of the participant flow showing for each group, the number of participants who were randomly assigned, received intended treatment, and were analyzed for the primary outcome will be provided, as recommended by the CONSORT 2010 statement.

Categorical variables will be reported as frequencies and percentages. Continuous variables will be expressed as mean ± SD or as median (Q_1_–Q_3_), according to the normality of their distribution, which will be tested with the Shapiro–Wilk test. Bartlett’s test will be performed to demonstrate homogeneity of variances between more than two groups. Primary endpoints will be assessed using the Student *t* test, if the samples are normally distributed or their variances are homogeneous; or Mann–Whitney U test, otherwise. P values will be corrected in order to account for the multiple endpoint. For the analysis of secondary variables, comparisons between continuous variables will be performed using the (paired or unpaired) Student *t* test or Mann–Whitney U test. The IMR at baseline, before PCI, and after PCI will be compared with an ANOVA for repeated measures or with the Friedman test, as appropriate. Comparisons between categorical variables will be evaluated using the Fisher exact test or the Pearson Chi square test, as appropriate. Correlations between continuous variables will be assessed using the Pearson or the Spearman rank correlation test. A 2-way ANOVA for repeated measures will be used to detect changes in IMR levels over time in the two study groups. Finally linear and logistic regression models will be carried out in order to identify predictors of periprocedural myonecrosis and delta-IMR. Analysis will be performed both in the full analysis set and a per protocol analysis and any differences between them would be the subject of explicit discussion and interpretation. In case of having multiple stenoses in some patient, additional adjusted analysis will be provided. Statistical analyses will be performed using the R statistical software [17] and p values <0.05 (2-tailed) will be considered significant. Whenever possible, estimates will be accompanied by confidence intervals.

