### P2Y_12_ receptors inhibitors: platelet reactivity and endothelial function

In patient with stable CAD, addition of Clopidogrel therapy results in an increase in endothelial function at the primary endpoint (assessed via reactive hyperaemic index) of 3 months. The improvement in endothelial function was already evident after 1 week of Clopidogrel therapy and seems to be not related to Clopidogrel effects on platelet aggregation [24].

On the other hand, among patients, those with T2DM exhibited increased platelet reactivity compared to patients without diabetes despite combined treatment with Clopidogrel and aspirin even when a loading dose of Clopidogrel rather than small daily doses was used [25]. The mechanisms leading to the high on-treatment platelet reactivity in T2DM patients are not fully elucidated and could potentially involved genetic factors [26].

Thus, after the introduction of new P2Y_12_ agents, the influence of Prasugrel or Ticagrelor on platelet reactivity in T2DM patients was object of studies demonstrating that Ticagrelor treated patients have overall lower platelet reactivity than patients on Prasugrel, independently of T2DM status or insulin treatment [27]. The effects of Prasugrel versus Clopidogrel on Coronary microvascular function in patients undergoing elective PCI was recently reported by Mangiacapra et al. [28] in the PROtecting MICROcirculation during coronary angioplasty (PROMICRO-2) trial. Compared with baseline, IMR increased post-PCI in the Clopidogrel group (p = 0.009), but not in the Prasugrel group (p = 0.299). Despite some limitations (small sample size; single time point measurement of IMR post-PCI; lack of intracoronary imaging for assessment of plaque burden) the result of this trial suggest that more intensive anti-platelet regimens might offer additional benefit compared with Clopidogrel also in the setting of elective PCI.

An ongoing randomised, prospective, controlled study [29] are also testing the effect of Clopidogrel, Prasugrel and Ticagrelor on multiple parameters of vascular function, platelet aggregation, oxidative and inflammatory stress before and up to 1 month after coronary artery stenting.

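### The mechanistic primary endpoint mixes starting a drug with switching or continuing one, because patients already on clopidogrel enter the trial and the primary test takes no account of prior use

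*Protocol article*

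**What the plan says.** In the protocol article, *Trial design and objectives* and Table 1 give the first primary endpoint as "Decrease in microcirculatory resistance caused by treatment onset", with a larger fall expected on ticagrelor.

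*Population recruitment and flow chart* gives newly treated patients a loading dose in both arms. It adds that patients already on daily clopidogrel "are allowed to enter the protocol", with no cap and no expected share. For them, "According to randomization arm these patients will be assigned, after baseline assessment of microcirculation, to continue Clopidogrel 75 mg/day or be switched to Ticagrelor", the switch being made with a loading dose. Their baseline IMR is therefore measured on clopidogrel. No loading dose is mentioned for those who continue.

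On allocation, the same section says: "The groups will be balanced according to the presence or absence of obesity". No other balancing factor is named.

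In *Sample size and statistical analysis*, "Primary endpoints will be assessed using the Student" *t* test, or the Mann–Whitney U test. Neither is adjusted. The factors named for attention are centre, baseline value of the primary variable, diabetes treatment, obesity, previous myocardial infarction and multiple stenoses. Prior clopidogrel is not among them. A regression for predictors of delta-IMR is planned, without listing the predictors.

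**The concern.** For a prior user allocated to clopidogrel, no treatment begins between the baseline and pre-PCI readings, so the endpoint as worded does not describe that patient. For a prior user allocated to ticagrelor, the measured change is a switch from one drug to another. Only untreated patients supply the comparison the endpoint names.

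Three things are at stake: what the mechanistic estimate means, whether its size depends on a case mix that nobody has planned, and some precision in a trial of 25 per group. The article gives one reason to think the issue is more than verbal. Its discussion of earlier work on clopidogrel reports: "The improvement in endothelial function was already evident after 1 week of Clopidogrel therapy". A prior user's baseline may thus already carry a vascular drug effect, although that study measured a reactive hyperaemic index, not IMR.

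**Working it through.** **Inputs from the article:** difference 10 and SD 10 in delta-IMR, two-sided alpha 0.025, 80% power, 20 evaluable per group, 25 enrolled per group.

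**Assumed, because the article gives neither:** *f*, the share already on clopidogrel, and *C*, the IMR fall on starting clopidogrel. *T* is the fall on starting ticagrelor.

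**1. The plan's own figure.** n per group = 2 × (2.241 + 0.842)² × (10/10)² = 19.01, rounded up to 20. The stated 20 reproduces. Power at 20 per group is 82.1% by the normal approximation and 79.3% by the noncentral *t*. The noncentral *t* is used below.

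**2. What is contrasted in each stratum.**

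| Patients | Ticagrelor arm, fall | Clopidogrel arm, fall | Contrast |
|---|---|---|---|
| Untreated | T | C | T − C |
| Prior users, clopidogrel effect lost on switching | T − C | 0 | T − C |
| Prior users, full ticagrelor effect added to the on-drug baseline | T | 0 | T |

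- In the second row the contrasts agree, and the pooled estimate is unbiased for T − C.
- In the third row the pooled estimate is (1 − f)(T − C) + fT = (T − C) + fC. With T − C = 10 this gives 10 + 0.2 × 2 = 10.4 up to 10 + 0.6 × 10 = 16.
- A related case: if clopidogrel loading lowers IMR by a further L units beyond maintenance and this persists to the pre-PCI reading, untreated controls have it and continuing controls do not. The pooled contrast is then overstated by f × L. The article gives no value for L.

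**3. Precision in the additive case.** Each arm is a mixture of two means that differ by C, so the variance of the change is 100 + f(1 − f)C², taking SD 10 as the within-stratum value.

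| f | C | Variance | SD | Power at 20 per group |
|---|---|---|---|---|
| – | 0 | 100 | 10 | 79.3% |
| 0.2 | 2 | 100.64 | 10.03 | 79.0% |
| 0.3 | 3 | 101.89 | 10.09 | 78.4% |
| 0.2 | 5 | 104 | 10.20 | 77.5% |
| 0.5 | 5 | 106.25 | 10.31 | 76.6% |
| 0.5 | 10 | 125 | 11.18 | 68.9% |

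**4. Chance imbalance in prior use.** The SD of the difference in shares at 20 per group is √(2f(1 − f)/20): 0.126 at f = 0.2 and 0.155 at f = 0.4 or 0.6. The chance that the arms differ by at least 20 percentage points is 16% (f = 0.2) to 26% (f = 0.4 or 0.6). A one-SD imbalance moves the contrast by C times that SD: 0.126 × 2 = 0.25 units up to 0.155 × 10 = 1.55 units. This is the variance of step 3 seen from another side, so the two must not be counted twice.

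**The case against.** The strongest reply is that endpoint (i) is a randomised comparison between arms. A within-arm fall that shrinks in controls is not the primary test, and if effects add the contrast is T − C in both strata. That stands. A reader might infer that the endpoint is biased in favour of ticagrelor. The article does not support this: bias needs non-additive effects or a lasting loading effect, and it documents neither. PCI is deferred at least 48 hours, about five half-lives by the article's account, so exposure in loaded and continuing clopidogrel patients may be similar by then.

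A reader might also infer a serious power loss. That too is unsupported. Nothing in the article shows that clopidogrel lowers IMR; the endothelial result concerns another measure at one week. A share of 0.5 maximises f(1 − f), and an effect of 10 equals the whole assumed difference between the drugs. If SD 10 already describes the mixed population, part of the loss is counted already. If switchers show the full ticagrelor effect, only the control arm is a mixture, and power at f = 0.5 with the contrast held at 10 is about 77.9% (C = 5) or 73.9% (C = 10).

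A covariate list may sit in a fuller analysis plan, and the unspecified regression could include prior use. This is fair, and absence of the covariate from a condensed article would be no finding alone. What remains is that the article fixes the endpoint wording, the eligibility of prior users and an unadjusted primary test, and these do not fit together.

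Endpoint (ii) is not implicated: both arms are on study treatment at its starting measurement.

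**Conclusion.** The point holds as a mismatch between the endpoint and the population admitted, not as a demonstrated bias. The endpoint definition in Table 1 and the handling of prior users in *Population recruitment and flow chart* need to be reconciled. As written, endpoint (i) averages two different contrasts, weighted by an unstated share of prior users.

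Its size rests on assumed inputs. If effects add and loading leaves no lasting effect, there is no bias, and the loss of power at 20 per group runs from 0.3 points (79.3% to 79.0%) to 10.4 points (79.3% to 68.9%) in a worst case. Milder inputs cost 2 points or less. If switched patients instead show the full ticagrelor effect, a contrast of 10 in untreated patients would read 10.4 to 16 over the assumed range. The article does not allow a choice between these cases, which is the reason to make the analysis able to show which applies.

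**What to change.** For endpoint (i) only:

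- Prespecify prior clopidogrel use (yes/no) as a covariate, alongside baseline IMR, in the primary comparison.
- Report the between-arm contrast descriptively in untreated and in pre-treated patients, with confidence intervals, and give the number of prior users by arm.
- Reserve the term treatment onset for untreated patients, and describe the comparison in prior users as switch versus continuation.

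The cost is wording in the analysis plan and one degree of freedom for prior use; concomitant medication is already recorded. Covariate adjustment removes the shift from chance imbalance, but it does not make the two contrasts equal if effects do not add; the stratum results are there to show that. They will be imprecise. If half the patients are prior users, about 10 to 12 untreated patients per arm remain, with power of about 44% to 53% for a difference of 10, so these results are supportive only.

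Balancing the randomisation on prior use as well as obesity is possible, but with about 50 patients in several centres it risks sparse cells, and it is not required. No change to treatment is proposed.
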